#### Steroid/anesthetic

Steroid injections will be prepared to include 20 mg Depo-Medrol and 2 mL 2% lidocaine.

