## Methods

### Study design

Prospective, randomized, controlled, double-blinded pilot trial evaluating the feasibility in relation to recruitment, retention, and acceptability of a single perineural PRP injection compared to that of steroid/anesthetic injection or injection with normal saline to the greater occipital nerve as a treatment for GON in patients following TBI. Flow through the study is portrayed in Fig. 1.

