### Interventions

Injections will be prepared as stated below. Patients will be asked to complete a numeric pain rating scale (NPRS) immediately pre- and post-injection. Patients will be asked to refrain from use of anti-inflammatory medications for 2 weeks prior to the injection and for 2 weeks following the injection due to the possible inhibitory effect on the action of PRP. Two 3 mL syringes with 2 mL of injectate (PRP, steroid/anesthetic, or normal saline) will be prepared for each participant. Patients will be assessed at the time of injection and will receive a single injection, if experiencing unilateral symptoms only, or two injections to each greater occipital nerve, if symptoms are bilateral. Patients will be monitored for 30 min following injection for any immediate adverse reactions, such as local reaction, increased pain intensity, anaphylaxis, nausea, or dizziness.

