#### Platelet-rich plasma

PRP will be prepared using the “Arthrex Angel System,” which is a fully automated PRP preparation machine. Sixty milliliters of blood will be drawn from the antecubital vein and processed via centrifugation. Five milliliters of sodium citrate will be added to the syringe prior to blood draw to prevent coagulation. Samples will be centrifuged as per manufacturer instructions, yielding 5 mL of PRP. For quality testing, 1 mL of PRP will be sent to the lab for analysis of platelet and leukocyte count, as compared to the patients’ whole blood. The remaining 4 mL of PRP will be divided into two syringes and 2 mL will be injected per symptomatic side.

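### The steroid/anesthetic recipe does not fit the 2 mL per syringe stated for all three arms, and the bilateral injection count does not fit the syringes prepared

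*Protocol article*

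**What the plan says.** All places are in the Methods of the protocol article.

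- **Interventions**, on volume: "Two 3 mL syringes with 2 mL of injectate (PRP, steroid/anesthetic, or normal saline) will be prepared for each participant". The steroid/anesthetic arm is named alongside the other two. The same section says that preparation follows the sections below it, so the recipe there is an operative instruction.
- **Platelet-rich plasma**: "Samples will be centrifuged as per manufacturer instructions, yielding 5 mL of PRP"; then "1 mL of PRP will be sent to the lab for analysis of platelet and leukocyte count"; then "The remaining 4 mL of PRP will be divided into two syringes and 2 mL will be injected per symptomatic side".
- **Normal saline**: the placebo is 2 mL.
- **Steroid/anesthetic**: "Steroid injections will be prepared to include 20 mg Depo-Medrol and 2 mL 2% lidocaine". No Depo-Medrol concentration, no final volume, and no indication whether the amounts are per side or per participant.
- **Interventions**, on the number of injections: one if symptoms are unilateral, or "two injections to each greater occipital nerve, if symptoms are bilateral".
- **Injection technique**: injections are bilateral when symptoms are bilateral. No count per nerve is given.
- **Blinding and randomization**: a research assistant prepares the 3 mL syringes and covers them with opaque tape to blind the injecting physician. The physician records a guess of the contents at the time of injection.

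**The concern.** Two sets of stated figures do not agree.

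**Volume.** The general statement and the PRP and saline sections all lead to 2 mL per syringe. The steroid/anesthetic recipe uses that volume for lidocaine alone and then adds a second product. The person preparing the syringe cannot both include everything listed and finish at 2 mL. If the recipe is followed in full, one arm alone has a different fill. Tape hides colour but may not hide plunger position, so the physician could have a cue to allocation. Volume would also be confounded with arm in the exploratory pain comparison. If instead only 2 mL of the mixture is drawn, the listed amounts are not delivered in full in the active comparator.

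**Number of injections.** Taken literally, a bilateral patient receives four injections, while two syringes are prepared and the PRP section gives 2 mL per side. This wording applies to every arm alike. What is at stake is consistent handling of bilateral patients, not the blind.

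**Working it through.** **Inputs from the protocol article.** Two syringes per participant with 2 mL of injectate (Interventions); PRP yield 5 mL, of which 1 mL goes to the laboratory (Platelet-rich plasma); saline 2 mL (Normal saline); 20 mg Depo-Medrol and 2 mL lidocaine (Steroid/anesthetic).

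**Assumption, not in the document.** Depo-Medrol concentration *c* of 20, 40 or 80 mg/mL.

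**1. Reproduce the plan's 2 mL.**
- PRP: (5 − 1) / 2 = 2.0 mL per syringe. Agrees.
- Saline: 2 mL. Agrees.

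**2. Recipe read per syringe.** Volume = 2 + 20/*c*. Because 20/*c* is positive, this exceeds 2 mL at any concentration; only the excess depends on *c*.

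**3. Recipe read per participant, over two syringes.** Volume per syringe = (2 + 20/*c*) / 2. This equals 2 mL only if 20/*c* = 2, that is *c* = 10 mg/mL, and falls short at any higher concentration.

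**4. Recipe mixed, but only 2 mL drawn.** Depo-Medrol delivered = 20 × 2 / (2 + 20/*c*) mg; lidocaine delivered = 2 × 2 / (2 + 20/*c*) mL.

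| Assumed *c* (mg/mL) | Volume of 20 mg (mL) | Per-syringe reading (mL) | Excess over 2 mL | Per-participant reading, each syringe (mL) | Delivered if 2 mL drawn |
|---|---|---|---|---|---|
| 80 | 0.25 | 2.25 | 12.5% | 1.125 | 17.8 mg, 1.78 mL lidocaine |
| 40 | 0.50 | 2.50 | 25% | 1.25 | 16.0 mg, 1.60 mL lidocaine |
| 20 | 1.00 | 3.00 | 50% | 1.50 | 13.3 mg, 1.33 mL lidocaine |

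**5. Basis of the amounts.** Per syringe, each treated side receives 20 mg and 2 mL lidocaine. Per participant, each side receives 20/2 = 10 mg and 2/2 = 1 mL. The readings differ twofold at any concentration.

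**6. Injections in a bilateral patient.** Prepared: 2 syringes × 2 mL = 4 mL.
- One 2 mL injection per nerve: 2 × 1 × 2 = 4 mL. Fits.
- Two full 2 mL injections per nerve: 2 × 2 × 2 = 8 mL. Twice what is prepared, and against "2 mL will be injected per symptomatic side".
- Two injections per nerve with each 2 mL split: 4 injections × 1 mL = 4 mL. Fits, but no splitting is described.

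**The case against.** The strongest reply is that the Interventions section already fixes 2 mL for the steroid/anesthetic arm by name, while the recipe only lists what an injection includes and gives no final volume. On that view nothing says that more than 2 mL is injected. This stands in part. A reader might infer that injected volume does differ by arm, but the document does not say so: the difference arises only if the recipe is given in full despite the stated 2 mL. The reply does not remove the conflict, because keeping to 2 mL means not delivering all of the listed amounts, and no discarding is mentioned.

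A reader might also infer that the physician's blind is broken. The document does not show that. Nothing establishes that a different fill would be noticed in a taped 3 mL syringe, and the guess questionnaire would help to detect a problem, although only afterwards. The pain outcomes are patient-reported, and fill volume offers no evident route to unblinding the patient.

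The shortfall under the per-participant reading depends on the assumed concentration; at 10 mg/mL it vanishes. The excess under the per-syringe reading does not depend on it.

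On the number of injections, the wording may simply be a slip for one injection to each nerve, which would use exactly the 4 mL prepared. It does not follow that 8 mL is intended. Nor is the Study design section's "a single perineural PRP injection" a contradiction: it is a summary phrase naming the intervention.

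Finally, a condensed article may leave preparation detail to the full protocol. That excuses what is absent, such as the concentration. It does not excuse stated figures that disagree.

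**Conclusion.** The point holds as a contradiction between stated figures, of moderate severity. The 2 mL per syringe reproduces for PRP and saline but not for steroid/anesthetic. Read per syringe, the recipe is over 2 mL whatever the concentration: 2.25 to 3.0 mL at an assumed 80 to 20 mg/mL. Read per participant, each syringe holds about 1.1 to 1.5 mL over the same assumed range. A difference in volume between arms, and with it a risk to the physician's blind, is conditional on the recipe being followed in full and has not been demonstrated.

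Separately, the bilateral wording in the Interventions section does not fit its own syringe count and the PRP section's volume per side unless each 2 mL is split. This affects all arms equally.

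No sample size, power or primary estimate changes. The primary outcomes are recruitment, attendance, retention and adverse events, analysed descriptively, and the comparison between arms is exploratory in 30 participants.

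**What to change.** The investigators should reconcile the Interventions, Platelet-rich plasma, Steroid/anesthetic, Normal saline and Injection technique sections so that:

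1. the steroid/anesthetic recipe and the stated volume per syringe agree;
2. the final volume per syringe is the same in all three arms;
3. it is clear whether the steroid/anesthetic amounts are per side or per participant;
4. the number of injections per symptomatic nerve is stated once and fits the syringes prepared.

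Which figures are right is for the trial's clinicians; none is proposed here.

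The Study status section says that recruitment and enrolment are under way. The team should therefore check how syringes have been prepared so far and, if practice has varied, take that into account when interpreting the exploratory comparison and the physicians' guesses.

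The cost is an amendment to the wording, matching instructions for whoever prepares the syringes, and a look back at participants already treated.

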#### Normal saline

Placebo injections will be with 2 mL normal saline.

### Injection technique

Given that ultrasound (US)-guided greater occipital nerve blockade demonstrated superiority over conventional blind technique in one study [39], participants will receive perineural injections under ultrasound guidance. Injections will be performed bilaterally if participants’ symptoms are bilateral; otherwise, they will be performed unilaterally. Where the greater occipital nerve is not visible under US, injection will be performed in accordance with conventional blind technique [40].

### Measures

Demographic information will be collected 2 weeks prior to starting the study including age, sex, weight/height, education, family history, past medical history, and medication use. Headache history will be collected including headache frequency, severity, as needed medication-use, type of headache, associated symptoms (i.e., paresthesia, fronto-orbital pain, nausea, vomiting), and headache triggers.

Questionnaires will be completed 2 weeks prior to injections, 1 week, 1 month, and 3 months post-injection. A daily headache diary provided via mobile application (Secure RedCap) available in iPhone or android device will be provided to record daily records of NPRS, headache frequency, and medication-use. Patients will complete daily headache diaries beginning at 2 weeks pre-injection and ending 3 months post-injection. See Figure 1 for a schematic of the study design.

### Primary outcomes

The primary outcomes of this trial will assess the feasibility of a double-blinded randomized control trial for the treatment of GON in patients with post-traumatic headaches. This pilot trial is a smaller version and will aim to inform a more extensive and larger version of this randomized control trial. Specific outcomes for evaluation will include the following:
Recruitment: Ability to recruit at least 30% of those patients screened for participation.Intervention attendance: At least 70% of those patients recruited for the study will attend and participate in the primary intervention.Retention: At least 70% of those receiving the primary intervention will complete the 3-month follow-up.Adverse events: Adverse events will be minimal. No more than 1 individual will have an adverse event. Any adverse event will be minor and reversible (i.e., nausea, light headedness, temporary pain at site of injection).

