**Methods:**

Thirty adults (over 18 years of age) with post-traumatic GON will be randomized into one of three groups: (1) autologous PRP injection, (2) steroid/anesthetic injection (standard care), or (3) placebo injection with normal saline. Injections will be performed to the greater occipital nerve under ultrasound guidance by a trained physician. Daily headache intensity and frequency data will be collected pre-injection and for the duration of the study period. Feasibility will be defined as greater than 30% recruitment, 70% completion of intervention, 70% retention, and less than 2 minor adverse events. Exploratory outcomes will be explored using the Headache Impact Test-6 (HIT-6, a valid and reliable 6-item questionnaire for assessment of the impact of headaches across different diagnostic groups of headaches) and the quality of life in following brain injury questionnaire (QOILIBRI).

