Multiple animal and in vitro studies have demonstrated PRP’s ability to assist in remyelination, axonal regeneration, and functional neurologic recovery in models of peripheral nerve injury [20, 23–32]. There have been few in vivo studies of PRP in treatment of peripheral neuropathies with variable success rates [33–37]. One randomized controlled trial found significant pain reductions in 60 patients with carpal tunnel syndrome and improvement of multiple markers of nerve function which persisted to 6 months following a single PRP injection [20]. Another clinical trial found significant improvement in pain following perineural PRP injections in patients with diabetic polyneuropathy [30].

These findings are encouraging as they reveal new therapeutic avenues in the management of peripheral nerve disorders. To our knowledge, PRP has not been investigated as a treatment for GON. We believe that PRP’s physiology, demonstrated efficacy, and safety profile make it an exciting and novel strategy to treat this debilitating condition. This study will investigate the feasibility of a randomized control pilot study for the treatment of GON in patients with post-traumatic headache using PRP. This pilot trial will evaluate the ability to recruit patients, retain patients throughout the protocol and the feasibility of implementing randomization using PRP for the treatment of patients suffering with GON following TBI. Our specific objectives are the following:
Evaluate the feasibility of a randomized pilot study of PRP as a treatment for patients with GON and post-traumatic headache in terms of recruitment (greater than 30%), attendance (70% intervention appointment attendance), retention (greater than 70% complete protocol), and acceptability of the protocol.Evaluate the safety profile of PRP for the treatment of GON in patients with post-traumatic headaches with less than 2 minimal adverse events.Exploratory objectives include evaluating whether patients with GON and post-traumatic headaches receiving PRP have significantly decreases pain, improved function, and quality of life, compared to patients receiving cortisone/anesthetic and normal saline injections.

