### Data management and monitoring

Participants will be assigned a study ID at the time of study enrolment. All identifying information will be removed once study participant numbers have been assigned and data is collected. Study data will be entered into a highly secure electronic REDCap database (REDCap 7.6.9 2020 @ Vanderbilt University). Only research team members will have access to this database. Paper copies of any data or participant information will be stored in a secure fashion. All data will be retained for 5 years following project completion in accordance with the University of Calgary Conjoint Health Research Ethics Board.

There will not be a formal data monitoring committee; a research assistant will periodically evaluate participant data for completeness and inform investigators of any issues. Adverse events will be reported via telephone or email, a research assistant will contact participants for further details at the time of reporting. A study physician will be alerted of any serious adverse events that require immediate attention.

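### The adverse-event feasibility criterion counts events in two places and individuals in a third, with unclear arm scope, so the same data can both pass and fail it

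*Protocol article*

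**What the plan says.** The article states the adverse-event criterion in three places.

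- **Abstract, Methods.** Feasibility is defined by four thresholds, the last being "less than 2 minor adverse events". The unit is events and no arm is named.
- **Background, specific objectives.** The second objective is: "Evaluate the safety profile of PRP for the treatment of GON in patients with post-traumatic headaches with less than 2 minimal adverse events". The unit is again events, and the sentence is about PRP.
- **Methods, Primary outcomes.** "No more than 1 individual will have an adverse event". The unit is persons and no arm is named. The next sentence adds: "Any adverse event will be minor and reversible (i.e., nausea, light headedness, temporary pain at site of injection".

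The Discussion repeats that adverse events are one of the four grounds on which feasibility will be judged. The Data analysis section plans descriptive statistics for all four. The sample is 30 randomized adults, allocated equally to three arms. No expected adverse-event rate is given, and no section reconciles the three statements.

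**The concern.** A feasibility threshold is useful only if two people applying it to the same data reach the same answer. Here they may not, because one may count events and the other persons, and one may count PRP patients and the other everyone. If the choice is left until the data are in, choosing the definition chooses the verdict on one of the four primary outcomes.

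A second issue is how demanding the rule is. The reactions named under Primary outcomes are minor and reversible, yet nothing excludes them from the count. Every arm has a needle at the occipital nerve and a 60 mL blood draw, so such reactions could arise in any arm. If they are not rare, a pooled limit of one person may well be exceeded in a trial that recruits, treats and retains its patients as hoped.

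**Working it through.** **Step 1. The three statements side by side.**

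| Place | Limit | Unit | Arm |
|---|---|---|---|
| Abstract, Methods | fewer than 2 | events (minor) | not named |
| Background, objectives | fewer than 2 | events (minimal) | not named, but the objective concerns PRP |
| Primary outcomes | at most 1 | individuals | not named |

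Fewer than 2 and at most 1 are the same whole number. The severity words are close in meaning. What remains is a clear difference in unit and an unclear scope.

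**Step 2. Two data sets that split the verdict.**

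- One PRP patient has nausea and site pain, and nobody else has an event. That is 1 individual, so Primary outcomes passes. It is 2 events, so the Abstract fails.
- Two saline patients each have brief site pain, and nobody else has an event. That is 2 individuals, so Primary outcomes (pooled) fails. There are 0 events in the PRP arm, so a PRP-only reading of the objective passes.

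**Step 3. How strict is the Primary outcomes rule?** The plan has no figure to reproduce. Let n be the patients counted and p the chance that a patient has any adverse event. With independent patients and the same p for all:

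P(pass) = (1 − p)^n + n·p·(1 − p)^(n−1)

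Inputs: n = 30 if all randomized patients are injected. n = 0.70 × 30 = 21 if the attendance criterion is only just met. n = 30/3 = 10 for one arm. The values of p are assumptions.

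Example, n = 30 and p = 0.10: 0.9^30 + 30 × 0.1 × 0.9^29 = 0.0424 + 0.1413 = 0.184.

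| Assumed p | n = 30 | n = 21 | n = 10 (one arm, counting individuals) |
|---|---|---|---|
| 1% | 96.4% | 98.1% | 99.6% |
| 2% | 88.0% | 93.5% | 98.4% |
| 5% | 55.4% | 71.7% | 91.4% |
| 10% | 18.4% | 36.5% | 73.6% |
| 20% | 1.1% | 5.8% | 37.6% |

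With 30 injected, the chance of passing is 80% at p of about 2.8%, 50% at about 5.5% and 5% at about 14.9%.

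The last column is not the pass probability of the Background objective, which counts events. A patient can have more than one event, so a limit on events among the same 10 patients would pass no more often than shown.

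**Step 4. What a pooled count says about PRP.** If the PRP arm has no events and each of the 20 control patients has a 10% risk, the pooled rule passes 39.2% of the time: 0.9^20 + 20 × 0.1 × 0.9^19. If instead the 10 PRP patients have a 20% risk and the controls none, it passes 37.6%. These are opposite situations for PRP, with nearly the same chance of passing.

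**Step 5. Precision when the limit is just met.** Exact (Clopper-Pearson) 95% intervals: 1/30 = 3.3% (0.1% to 17.2%); 1/10 = 10% (0.3% to 44.5%).

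**The case against.** The strongest reply is that this is loose drafting around one intended limit, and that much of the rest depends on rates nobody has supplied. Several parts of it stand.

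- The whole-number limit is the same throughout, so a reader who infers three different thresholds goes too far. The objective never says that only the PRP arm is counted; that scope is a reading of it.
- The pass probabilities depend on p. At 1% or 2% the pooled rule is comfortable, and with 21 injected it is milder. The Interventions section lists reactions to watch for but gives no frequency, so the article does not establish that such reactions are common.
- A pooled count is defensible as a measure of trial burden. The blood draw and injection are part of the trial in every arm, and the first two objectives treat feasibility and PRP safety separately.
- A reader might infer that failing this one line stops the larger trial. The Abstract joins the four criteria and the Discussion repeats them, but the planned analysis is descriptive and no section states such a stopping consequence.
- A reader might also infer that passing depends on who volunteers a report, from "Adverse events will be reported via telephone or email". That sentence gives a channel. Patients are also watched for 30 minutes after injection, and collection forms are detail that an article may leave to the full protocol.

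None of this removes the difference in unit, or tells the reader which arms count.

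**Conclusion.** The point holds as an inconsistency in a stated primary outcome. Events and individuals give opposite verdicts on simple, plausible data, and so can pooled and PRP-only counting. This follows from the text and needs no assumption about rates.

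The strictness of the pooled rule is a second, conditional finding. Pooling is the natural reading of Primary outcomes, though it is not stated. With all 30 injected, the chance of passing falls from 96% at an assumed risk of 1% to 18% at 10%; with 21 injected it is 36.5% at 10%. These figures assume independent patients with a common risk.

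It would be tempting to conclude that the criterion will reject a feasible trial. The documents do not support that, because they give no rate. They support only that it could, and that a pooled pass or fail is weak evidence about PRP.

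**What to change.** Replace the statements in the Abstract, the Background objective and Primary outcomes with one criterion, fixed before the data are seen. It should state:

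- the unit, which should be individuals;
- the arm or arms counted;
- which events count, and explicitly whether minor reversible events count toward pass or fail;
- the numeric limit.

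Whatever limit is kept, report individuals with any adverse event by arm with exact 95% confidence intervals, so that events in the control arms are not read as evidence about PRP.

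If minor reversible events are set apart, name them one by one. The monitoring list under Interventions should not be adopted whole as expected transient reactions, because it reads "any immediate adverse reactions, such as local reaction, increased pain intensity, anaphylaxis, nausea, or dizziness" and so includes anaphylaxis.

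The cost is a wording change, made as a protocol amendment because the trial is already recruiting, and by-arm intervals that will look wide: with 1 of 10 affected, 0.3% to 44.5%. That width is an honest picture of what ten patients per arm can show.
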